## Abstract

**Background:**

One of the challenges in treating patients with heart failure (HF) is achieving clinical stability and reducing the hospital readmission rate. A diuretic dose adjustment algorithm developed in the United States (Diuretic Treatment Algorithm, DTA) and later validated for use in Brazil (as the Algoritmo de Ajuste de Diurético, AAD) has proved feasible and readily applicable, but its effect on clinical outcomes has yet to be assessed. This report aims to describe a randomized clinical trial protocol designed to assess the effectiveness of the AAD and of nonpharmacologic management in improving clinical stability and reducing the readmission rate at 90 days in patients with HF.

**Methods/Design:**

A PROBE (prospective randomized open blinded endpoint) parallel-group design will be used. Adult patients with a diagnosis of reduced ejection fraction HF, who are being treated at a specialized HF clinic are being recruited. Those with indications for loop diuretic dose adjustment during routine clinic visits will be randomized to take part in the trial. Participants in the intervention group (IG) shall have their diuretic doses adjusted in accordance with the AAD and receive four telephone calls (one per week) over 30 days to reinforce guidance on nonpharmacological management (fluid and sodium restriction). Participants in the control group (CG) shall have their diuretic doses adjusted by a physician during the first trial visit and shall not receive any telephone calls. Patients in both groups shall return at 1 month for face-to-face reassessment. The study endpoints shall comprise readmission and/or emergency department visits due to HF decompensation within 90 days and clinical instability. All participants shall be required to have a scale at home (or easy access to one), a telephone number, agree to telephone-based follow-up, and be available to return for a 1-month trial visit. Overall, 135 patients are expected to be enrolled in each group.

**Discussion:**

This trial shall assess the effectiveness of the AAD algorithm and non-pharmacologic management by early identification of clinical deterioration and establishment of a combined intervention to reduce emergency department visits, readmission rate, or a composite endpoint thereof.

**Trial registration number:**

ClinicalTrials.gov Identifier, NCT02068937 (23 February 2014).

## Background

Heart failure (HF) is a highly prevalent clinical syndrome. In the United States alone, more than 5 million people have HF and more than 550,000 new cases are diagnosed each year. Complex issues involving physiological, psychological, social, and medical care make management of HF a challenge [1,2]. Over the last years, the annual number of hospitalizations with HF as a primary cause increased from 800,000 to over 1 million, and that of hospitalizations with HF as a secondary diagnosis, from 2.4 million to 3.6 million [3]. Approximately 50% of these patients are readmitted to hospital within 6 months of discharge, and 70% of these readmissions are associated with deterioration of HF [4,5]. The prevention of HF-related readmission has been the focus of several studies, and efforts are being made to reduce this rate to the 20% range [6].

There is a consensus in the literature that HF-related readmissions are prompted mainly by clinical decompensation due to congestive processes. The main manifestations of this decompensation are dyspnea, fatigue, lower extremity edema, paroxysmal nocturnal dyspnea, orthopnea, and jugular venous distension [7]. These signs and symptoms of decompensation are readily recognizable in a variety of settings, which enables rapid intervention by healthcare professionals. Several different care processes have the potential to reduce HF-related readmission rates, including comprehensive educational intervention during hospital admissions, medication reconciliation, support from the nursing team after hospital discharge, disease management, and improvement of communication between patients and providers [8]. One strategy that has been used as an adjuvant to conventional treatment is telemonitoring. This strategy, which has proven cost-effectiveness and can be implemented in different settings [9], enables early identification of clinical deterioration and prompt intervention, and has been demonstrated to reduce the risk of hospitalization for decompensated HF and reduce all-cause mortality [10-12].

Within this context, United States (U.S.) researchers developed an algorithm for over-the-phone adjustment of diuretic doses, with a focus on pharmacological and nonpharmacological assessment and home-based management of patients with HF. The Diuretic Treatment Algorithm (DTA) was demonstrated to be effective in preventing HF decompensation, significantly reducing 30-day readmission rates and decreasing HF-related hospitalizations by 50% [13]. The DTA was later translated and adapted for use in Brazil as the Algoritmo de Ajuste de Diurético (Diuretic Adjustment Algorithm, AAD) and validated in an outpatient sample [14]. The results of that study demonstrated the feasibility and applicability of the AAD in the Brazilian healthcare reality. However, the effects of use of this algorithm on clinical outcomes have yet to be tested.

The present report aims to describe a randomized clinical trial (RCT) protocol designed to assess the effectiveness of the AAD and of nonpharmacologic management in improving clinical stability and reducing the 90-day readmission rate in patients with HF.

## Methods/Design

### Study design

A PROBE (prospective randomized open blinded endpoint) parallel-group design shall be employed, with patients recruited from the specialty HF clinic of Hospital de Clínicas de Porto Alegre (HCPA), a university-affiliated hospital in Porto Alegre, Rio Grande do Sul, Brazil. Clinical assessment shall take place at the HCPA Clinical Research Center.

### Inclusion and exclusion criteria

Adult patients with a diagnosis of reduced ejection fraction HF who are being treated at a specialized HF clinic are being selected. The diagnosis of HF is established by clinical history (signs and symptoms), echocardiographic findings (left ventricular ejection fraction <45%) [15] and medical records confirming management at the HF clinic. Patients are required to have a medical indication for adjustment of loop diuretic (furosemide) dose during a clinic visit, have a scale at home or ready access to one, have a telephone number for follow-up contact, agree to receive such follow-up and be available to return to the hospital for a 1-month reassessment visit. The exclusion criteria are communication barriers or physical impairments that preclude body weight monitoring, degenerative neurological conditions, waitlist status for cardiac transplantation, scheduled surgery and chronic kidney disease requiring renal replacement therapy.

### Ethical considerations

All participants will read and sign an informed consent form before entering the study. The study protocol was approved by the HCPA Institutional Review Board (protocol number 10-0376) and will be conducted in accordance with the principles of the Declaration of Helsinki and in compliance with the Brazilian legal and regulatory framework for research involving human subjects.

### Heart Failure Clinic and team approach

The trial HF clinic is staffed by a multidisciplinary team of cardiologists, nurses, and dietitians. On average, 200 patients per month are seen at the clinic, with a focus on promoting adherence to optimized pharmacological and nonpharmacological management. During each visit, patients undergo a clinical assessment that includes use of the Clinical Congestion Score (CCS) [16]. All interventions seek to improve the health education process and enable implementation of self-care interventions with family support.

### Sample size

Sample size was estimated in the WinPepi 11.1 software suite, using readmission or emergency department visit within 90 days of randomization as the endpoint [16]. Considering a 20% relative reduction in readmissions or emergency department visits in the intervention group, a significance level of 0.05, a statistical power of 80%, and an attrition rate of 20%, the sample size was set at 270 patients (135 in each group).

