### Statistical analysis

Continuous variables shall be expressed as means and standard deviations if normally distributed or medians and quartiles otherwise. Categorical variables shall be expressed as absolute and relative frequencies. Depending on the distribution of variables, baseline characteristics and the effect of the trial intervention shall be compared by means of Student’s *t-*test or the Mann-Whitney *U* test (for continuous variables) or Pearson’s chi-square test (for categorical variables). A *P* value <0.05 (two-tailed) shall be considered statistically significant. Intention-to-treat analysis shall be employed for all patients who meet a trial endpoint before 90 days. All statistical analyses shall be carried out in Statistical Package for the Social Sciences (SPSS) 18.0.

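### The stated 270 patients give 80% power for a 20% relative reduction only if about 83% of controls have an event within 90 days

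*Protocol article*

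**What the plan says.** The Sample size section sizes the trial on a binary endpoint, readmission or emergency department visit within 90 days of randomization. The effect is given as "Considering a 20% relative reduction in readmissions or emergency department visits in the intervention group". The remaining inputs and the result follow in the same sentence: significance level 0.05, power 80%, then "an attrition rate of 20%, the sample size was set at 270 patients (135 in each group"). The calculation was done in WinPepi, and no control-group event rate is given.

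The Statistical analysis section fixes the sidedness: "A *P* value <0.05 (two-tailed) shall be considered statistically significant". It names Pearson's chi-square test for categorical variables.

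The nearest thing to a baseline rate is in the Background: "Approximately 50% of these patients are readmitted to hospital within 6 months of discharge". The same paragraph attributes 70% of those readmissions to worsening HF.

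**The concern.** A 20% relative reduction in a proportion is a small absolute difference unless the control rate is very high: 10 points at a control rate of 50%, 6 points at 30%. Differences of that size normally need several hundred patients per group or more, so 135 per group looked too few.

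If the numbers do not fit, the published 80% power is a property that the design does not have for the effect it names. A reader of a later non-significant result could then take a 20% relative reduction to have been tested with adequate power when it was not.

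**Working it through.** **Inputs from the article.** Intervention rate p2 = 0.8 × p1 (20% relative reduction); alpha 0.05, two-sided (z = 1.960); power 80% (z = 0.842); 135 per group randomized; 20% attrition, so 135 × 0.80 = 108 evaluable per group.

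**Input not in the article.** The 90-day control rate p1. I scan it and label the results as assumption-based.

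**Formulas** (two proportions, pooled variance under the null, p̄ = (p1 + p2)/2):

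- n per group = [1.960·√(2p̄(1−p̄)) + 0.842·√(p1(1−p1) + p2(1−p2))]² / (p1 − p2)²
- enrolled per group = n / 0.80
- power = Φ{[(p1 − p2)·√n − 1.960·√(2p̄(1−p̄))] / √(p1(1−p1) + p2(1−p2))}

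**Can 135 per group be reproduced?** Solving power = 0.80 with p2 = 0.8·p1 gives p1 ≈ 0.83 at n = 108 and p1 ≈ 0.78 at n = 135. Across variants (continuity correction or not; attrition as n/0.8, as n × 1.2, or ignored), two-sided calculations return about 135 only for control rates of roughly 77% to 86%. Even a one-sided calculation needs at least about 71%.

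**Worked case, p1 = 0.50, p2 = 0.40, p̄ = 0.45.**

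- n = (1.379 + 0.589)² / 0.01 ≈ 388 per group; 388/0.80 = 485 enrolled per group, 970 in total.
- Power at 108: (0.10 × 10.392 − 1.379)/0.70 = −0.485, and Φ(−0.485) = 0.314.

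**Scan, 20% relative reduction:**

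| Assumed control rate | Evaluable n per group for 80% power | Total with 20% attrition | Power, 108 per group | Power, 135 per group |
|---|---|---|---|---|
| 20% | 1447 | 3618 | 12% | 13% |
| 30% | 859 | 2148 | 17% | 20% |
| 40% | 564 | 1410 | 23% | 28% |
| 50% | 388 | 970 | 31% | 38% |
| 60% | 270 | 676 | 42% | 51% |
| 70% | 186 | 466 | 57% | 67% |
| 80% | 123 | 308 | 75% | 84% |

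**What 108 per group can detect at 80% power:** 30% to 14.3% (52% relative), 40% to 22.4% (44% relative), 50% to 31.4% (37% relative).

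**Effects that roughly reproduce 135 per group:**

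- A 20-point absolute reduction, 60% to 40%: 97 per group, or 107 with continuity correction; 107/0.80 ≈ 134. Without the correction it is at most 122 per group at any control rate. At 40% to 20% it gives only 114 even with the correction.
- A halving, 33% to 16.5%: 107 per group without correction; 107/0.80 ≈ 134. From 35% to 17.5%: 110 with correction; 110/0.80 ≈ 138.

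**The case against.** The strongest reply is that the article gives no control rate, so the authors may have used a high one. The Background figure counts readmissions after discharge. The trial endpoint also counts emergency department visits, and the trial enrols outpatients who need a diuretic change, so 50% at 6 months is not a direct benchmark. The source cited for the sizing endpoint is not available here, and a condensed article may leave the rate to the full protocol. Part of this stands. The omission is not itself the fault, and the 12% to 42% range depends on my assumed rates of 20% to 60% and on full 20% attrition.

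It does not rescue the sentence. The article offers nothing that supports about 80% of controls having an event within 90 days. Its own Endpoints section limits events to those due to HF decompensation, over half the benchmark's time span. Even at 60%, above the 6-month figure, power is 42%, or 51% with no attrition.

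A reader might infer that the authors entered a 20-point absolute reduction and miswrote it as relative. The article does not support that as a conclusion. It never mentions an absolute reduction, and the match needs a continuity correction, division by 0.8 and a control rate of about 52% to 68%. A halving from about 33% to 35% fits about equally well, and the Background reports that the original algorithm cut HF-related hospitalizations by 50%. Neither origin can be established.

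**Conclusion.** The statement is wrong as written. A 20% relative reduction, two-sided alpha 0.05, 80% power, 20% attrition and 135 per group are mutually compatible only at a control rate of about 83% (about 78% with no attrition). That finding needs no assumed control rate.

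The size of the shortfall does need one. The 12% to 42% range with 108 evaluable per group (13% to 51% with 135) holds for assumed control rates of 20% to 60%, and power would be higher if the true rate were higher still. That such rates are out of reach is a judgement based on the article's single 6-month benchmark, which is not the same endpoint or population. The cause of the mismatch stays open.

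**What to change.** Keep N = 270. In the Sample size section, state the assumed 90-day control rate and whether the reduction entered in WinPepi was relative or absolute. Then correct the sentence in one of two ways:

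1. Give the effect that 108 evaluable patients per group detect with 80% power at that control rate (for example 30% to 14.3%, 40% to 22.4%, or 50% to 31.4%); or
2. Keep the 20% relative reduction and state its true power at that control rate.

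Under either option, add that a non-significant result will not by itself exclude a 20% relative reduction.

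The cost is a short correction and no extra patients. Recruitment was still open at publication (66 enrolled), so this can be done before results are known. The downside is that the stated planning effect or power becomes less favourable. Enlarging the trial to support the 20% relative reduction would take 676 to 3618 patients at control rates of 60% down to 20%, which is why restating the claim is the proportionate remedy.

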### Study protocol

Participants randomized to the CG shall have their diuretic dose adjusted at the physician’s discretion. These patients will not receive telemonitoring, but will return for 30-day clinical reassessment.

Participants randomized to the IG shall receive telemonitoring with the AAD for dose adjustment and CCS for assessment of signs and symptoms of decompensation and body weight fluctuations. Telephone calls shall take place once weekly for a total of four calls during the 1-month intervention period. First, the calling nurse shall enquire as to the presence of signs and symptoms of deterioration (paroxysmal nocturnal dyspnea, orthopnea, fatigue during activities of daily living (for functional class assessment), lower extremity edema, vomiting or diarrhea, dizziness or syncope, and body weight fluctuations) during the preceding week. Depending on the signs and symptoms reported, the patient shall receive guidance according to one of the following algorithm pathways: weight remained within the expected range (change in body weight <1 kg), weight loss was greater than expected (weight loss ≥1 kg), or weight gain was greater than expected (weight gain ≥1 kg). Guidance shall be provided in accordance with the patient’s individual needs regarding adherence to pharmacological and nonpharmacological management. A face-to-face reassessment shall be conducted at 30 days by a nurse blinded to group allocation. At each telephone contact/reassessment, the AAD shall be administered again to guide diuretic dose adjustment.

Data on clinical and sociodemographic parameters shall be collected from all participants in both groups, with the CCS used to assess clinical condition.

During clinic visits, all patients are provided routine guidance on HF, including information on pharmacological management (regular use of prescribed medications and their effects) and nonpharmacological management (weight management, fluid and sodium restriction, physical activity), and any questions they may have are answered.

At the 30-day visit, all patients shall undergo reassessment by means of the CCS and recollection of data on all variables of interest.

At 90 days, the study endpoint (readmission or emergency department visit, change in CCS, deterioration in NYHA functional class, and HF-related mortality) shall be assessed by means of a chart review, consisting of an analysis of patients’ records. Patients who sought care at an outside facility shall be asked to provide their progress notes or discharge summary. Chart-based endpoints are expected to be confirmed by telephone contact with participants in both groups (Figure 1).

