### Endpoints

The endpoints include hospital readmission and/or emergency department visits due to HF decompensation within 90 days, two-point change in CCS, and deterioration of NYHA functional class. The secondary outcome shall be a composite of the aforementioned primary endpoints and 90-day HF-related mortality.

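### The day-30 assessor of CCS and NYHA is meant to be blinded, but the plan also places the AAD in that reassessment without separating the two tasks

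*Protocol article*

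**What the plan says.** The Study design section of the Protocol article sets the framework: "A PROBE (prospective randomized open blinded endpoint) parallel-group design shall be employed". Treatment is open, and the protection against assessor bias is that endpoints are judged blind.

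The Study protocol section then makes two consecutive statements about the 30-day visit:

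- On who runs it: "A face-to-face reassessment shall be conducted at 30 days by a nurse blinded to group allocation".
- On what is done there, in the sentence that follows directly: "At each telephone contact/reassessment, the AAD shall be administered again to guide diuretic dose adjustment".

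The same section ties the algorithm to one arm: "Participants randomized to the IG shall receive telemonitoring with the AAD for dose adjustment and CCS for assessment of signs and symptoms of decompensation". Of controls, the abstract says that they "shall have their diuretic doses adjusted by a physician during the first trial visit and shall not receive any telephone calls". Controls nevertheless come to the same visit: "These patients will not receive telemonitoring, but will return for 30-day clinical reassessment". What is done there is common to both arms: "At the 30-day visit, all patients shall undergo reassessment by means of the CCS and recollection of data on all variables of interest".

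The Endpoints section lists, beside readmission or emergency visits within 90 days, a "two-point change in CCS, and deterioration of NYHA functional class".

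**The concern.** The AAD is the core of what is being randomised. If it is part of a reassessment run by a nurse who should not know the allocation, her own task list gives the allocation away: a patient for whom she applies the algorithm is in the intervention group, and one for whom she does not is a control.

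She is also the person who records the CCS and NYHA class. Both depend on the examiner. According to the Discussion, the CCS is built from findings such as crackles, jugular venous distension, third heart sound, orthopnea and oedema, together with functional class. An assessor who knows the allocation can shade such items without intending to. In a PROBE trial, where patients and treating staff already know the arm, little else guards against this.

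The secondary outcome would inherit the problem, because it combines the listed endpoints with HF-related mortality.

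**Working it through.** The plan gives no figure on this point to reproduce. The check sets the statements side by side.

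1. **Who conducts the visit.** A nurse blinded to allocation (Study protocol).
2. **What happens at reassessment.** The AAD is applied again to guide the diuretic dose (Study protocol, next sentence). Elsewhere the article uses the word reassessment for the in-person one-month visit (abstract; Inclusion and exclusion criteria; Study protocol), and this sentence directly follows the one on that visit. The natural reading therefore includes day 30.
3. **Who receives the AAD.** The intervention group. Control doses are set by a physician (abstract; Study protocol).
4. **Who attends and is scored.** Both arms, with the CCS.
5. **Consequence of 1 to 4.** If the assessing nurse carries out step 2 in the intervention group only, she has to know the allocation. If she does so before or during scoring, the scores are not blinded. Only a separation of person or of order prevents this, and the article states neither.
6. **Less likely alternative.** If the AAD were applied to everyone at day 30, the nurse could stay blinded, but controls would receive the tested algorithm once within the 90-day window. The wording speaks against this: the sentence closes the intervention-group paragraph, and *again* does not fit patients who have not had the algorithm before.
7. **Which endpoints are exposed.** The only face-to-face trial visit scheduled after baseline is the one at 30 days. The 90-day endpoints come from chart review confirmed by telephone (Study protocol), so no new trial examination is scheduled that could correct a biased day-30 score. Readmission and emergency visits, the endpoint used in the Sample size section, do not come from scoring at the 30-day visit and so are largely unaffected by a lost blind there.
8. **How much of the trial can still be protected.** Planned: 270 (Sample size). Enrolled: 66 (Trial status). Not yet enrolled: 270 − 66 = 204, and 204 / 270 = 0.756, about three quarters of the planned sample.

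**The case against.** The strongest reply is that the two sentences are compatible. The AAD sentence is passive and names neither an actor nor an order. The blinded nurse could score while a colleague runs the algorithm, or scoring could come first. The article mentions a calling nurse and a multidisciplinary clinic team, so the staff exist. The flowchart is not shown, and a condensed article may leave visit logistics to the full protocol. Last, the term in the AAD sentence could mean reassessment by telephone only.

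Much of this stands. A reader might infer that the two sentences flatly contradict each other; they do not. A reader might also infer that every day-30 score is unblinded. That would require the assessing nurse herself to apply the AAD, and to do so before she scores, and the article says neither.

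What does not stand is that the matter is only an omitted detail. The article states who runs the visit and also that the algorithm is applied at reassessment. Put together without any separation, those statements describe a visit that compromises its own blind. The telephone-only reading does not fit how the article uses the word elsewhere. The point that the sentence belongs to the intervention-group paragraph weakens the idea that controls receive the AAD, but it strengthens the main concern, because use in one arm only is what reveals the allocation.

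**Conclusion.** The concern holds in a limited form. As written, the 30-day visit puts the blinded assessor and the allocation-revealing intervention together, and so undermines the blinded-endpoint property for CCS change and NYHA deterioration. This rests on two assumptions: that the reassessment in the AAD sentence includes the 30-day visit, and that the day-30 scores feed the CCS and NYHA endpoints. The size of any resulting bias cannot be derived from the document.

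Two further inferences are tempting and are not supported. One is that controls are treated with the AAD for the remaining 90 − 30 = 60 days and that the treatment difference shrinks in proportion. At most the wording allows one application at day 30. The intervention is four weekly calls within one month, and no AAD contact is scheduled later in either arm. If controls did receive it, the contrast would be reduced by an amount that the document does not allow anyone to quantify. The other is that the 90-day chart review is also unblinded; the article does not say so.

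The change is worth making because it is cheap and protects the main safeguard of an open trial.

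**What to change.** State in the Study protocol section that at day 30:

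- the blinded nurse records and locks CCS and NYHA class first and takes no part in the AAD;
- any AAD step in the intervention group follows that lock and is handled by the calling nurse, who already knows the allocation because only that arm is telephoned;
- patients are asked not to mention telephone calls before scoring is complete.

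The sponsor should also reconcile the two sentences by stating which arm receives the AAD at day 30. This review takes no position on how doses should be adjusted in either arm.

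The cost is a small scheduling burden: tasks at an existing visit are reordered, and the calling nurse must be available after scoring.
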